### **The Global Rating of Change Scale**

This is a self-reported measure of patients' perceived change. It will be administered prior to the performance-based assessments preoperatively, prior to discharge, 4 weeks and 3 months postoperatively. Participants will be asked: 'Overall, how do your arms function now, compared with how your arms functioned at the initial assessment before surgery?' Responses will be recorded according to a 7-point scale from 'very much improved' to 'very much worse'. It has been previously reported that when participants rate their change as 'minimally improved', 'no change' or 'minimally worse', it is unlikely that a clinically important difference has occurred;

therefore, these patients are grouped into an ‘unchanged’ category [56]. Responses of ‘much worse’, ‘very much worse’, ‘much improved’ and ‘very much improved’ indicate a clinically important difference has occurred and therefore these patients are grouped into a ‘changed’ category [56].

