## Statistical analysis

The analysis will follow the intention-to-treat, whereby all participants will be analyzed according to the groups to which they were originally randomized, regardless of their adherence to the intervention protocol. SPSS version 27.0 will be used to analyse all collected data. Missing data will be handled using multiple imputation, which creates several datasets by statistically estimating missing values and then combines the results to account for uncertainty. This method is preferred over last observation carried forward, as it reduces bias and more accurately reflects variability in clinical studies [61].

Descriptive statistics will summarize participants' baseline demographic and clinical characteristics. Continuous variables will be reported as mean (standard deviation, SD) or median (interquartile range, IQR) depending on the distribution, while categorical variables will be reported as frequency (percentage). Baseline comparability analysis of the clinical outcomes between groups will be performed using independent *t*-tests for continuous variables and Chi-square tests for categorical variables.

The primary outcomes (6MWT and MIP) and secondary outcomes (1MSTS, SPPB, hand grip strength, FSS, Bio-impedance Test, EuroQol, SAQ and Global Rating of Change Scale) will be measured at multiple time points: baseline, post-prehabilitation (4 weeks), before hospital discharge, and at 4 and 12 weeks postoperatively. To evaluate changes over time and between-group differences, a linear mixed-effects model (mixed model ANOVA) will be employed, provided the assumptions of normality and sphericity are met. Normality will be evaluated using the Kolmogorov–Smirnov test, while sphericity will be assessed using Mauchly's test. Mixed model ANOVA will provide results for time effect, group effect, and time-group interaction effect. Statistically significant time effect and group effect indicates significant within-group changes and between-group difference respectively, while significant time-group interaction effect determine if the interventions yield the desired effect on the dependent variables. Post hoc pairwise comparisons will be conducted using Bonferroni correction where appropriate.

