| 1 Minute Sit to
Stand (1MSTS)                                 |                                |                                 |              | X                                   | X                                             | X                                 | X                            |
| Hand grip Test                                                   |                                | X                               |              | X                                   | X                                             | X                                 | X                            |
| Bio-impedance Test                                               |                                | X                               |              | X                                   | X                                             | X                                 | X                            |
| Fatigue Severity
Scale (FSS)                                  |                                | X                               |              | X                                   | X                                             | X                                 | X                            |
| the Hospital Anxiety
Depression Scale
(HADS)               |                                | X                               |              | X                                   | X                                             | X                                 | X                            |
| Euro QoL (EQ-5D-
5L)                                          |                                | X                               |              | X                                   | X                                             | X                                 | X                            |
| Self-Administered
Physical Activity
Questionnaire
(SAQ) |                                | X                               |              | X                                   | X                                             | X                                 | X                            |
| Global Rating of
Change (GRC)                                 |                                | X                               |              | X                                   | X                                             | X                                 | X                            |

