### *Global Rating of Change Scale*

How does your function now, compare to your function at the initial assessment before surgery?

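### Fig. 1 omits the baseline 1-minute sit-to-stand that the analysis needs, and the Global Rating of Change is timed, worded and grouped inconsistently

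*Protocol*

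**What the plan says.** The Statistical analysis section of Phase 2 lists the "secondary outcomes (1MSTS, SPPB, hand grip strength, FSS, Bio-impedance Test, EuroQol, SAQ and Global Rating of Change Scale" and states that they "will be measured at multiple time points: baseline, post-prehabilitation (4 weeks), before hospital discharge, and at 4 and 12 weeks postoperatively". For the analysis, "To evaluate changes over time and between-group differences, a linear mixed-effects model (mixed model ANOVA) will be employed", reporting time, group and time-group effects, and the interaction is what decides whether the intervention worked. The section also says "Baseline comparability analysis of the clinical outcomes between groups will be performed using independent" t-tests (chi-square for categorical variables). The Abstract (Methods) likewise has patients assessed at baseline and names the sit-to-stand test among the outcomes.

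Fig. 1 differs. Its row "1 Minute Sit to Stand (1MSTS") is blank at baseline and marked at the four later visits. Its row "Global Rating of Change (GRC") is marked at baseline and at all four later visits.

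The section on the Global Rating of Change Scale gives four administrations, the first preoperative. It words the item as "Overall, how do your arms function now, compared with how your arms functioned at the initial assessment before surgery"; the appendix form asks "How does your function now, compare to your function at the initial assessment before surgery". The same section sorts the seven responses into two categories: the three central ones are *unchanged*, and the two at each end, worse and improved alike, are together *changed*.

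**The concern.** The schedule table is what staff work from at a visit. A 1MSTS value not taken before training starts cannot be obtained afterwards, and recruitment runs from February 2025 to July 2026.

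For the GRC the problem is one of meaning. A scale that asks about change since the initial assessment has nothing to refer to at that assessment. Two different item wordings measure two different things. A category that holds both marked improvement and marked deterioration cannot tell a patient who benefited from one who was harmed. That matters if it is used as an outcome, or as the anchor for the clinimetric (MCID) aim in research question 1.24 and secondary objective iv.

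**Working it through.** No sample-size or power figure is involved, so the check compares the sections and follows each instruction through to the analysis.

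**1. 1MSTS visits.** The Statistical analysis section gives five: baseline, post-prehabilitation, pre-discharge, 4 weeks, 12 weeks. Fig. 1 marks four, without baseline. The row has a full set of eight cells (label plus seven columns), and its other marks sit under the right headers, so a shifted column does not explain the blank. Every other outcome row in Fig. 1 has a baseline mark.

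**2. Effect on the planned test.** Suppose HIIT produces a 1MSTS gain of *d* repetitions over MICT during prehabilitation, and it is kept equally afterwards.
- With baseline, the expected arm differences over five visits are 0, *d*, *d*, *d*, *d*. They vary over time, so there is a time-group interaction.
- Without baseline, they are *d*, *d*, *d*, *d*. They do not vary, so the interaction is zero whatever the size of *d*.

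In the second case the benefit shows only as a group effect, with no pre-training value to set it against, and the protocol's interaction criterion would miss it. The planned multiple imputation cannot fill the gap: if no patient has a baseline 1MSTS, there are no observed values to impute from.

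**3. GRC visits.** The Statistical analysis section and Fig. 1 give five, including baseline. The scale's own section gives four, from the preoperative visit on. At baseline the answer is either undefined or no change for everybody. In the latter case the within-arm variance is zero, so the planned baseline t-test has no denominator, and the baseline level carries no information on patients for the mixed model.

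**4. GRC wording.** The scale's section asks about arm function; the appendix form asks about function in general. The reference point is the same, but the construct is not. The primary outcomes are walking distance and inspiratory pressure.

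**5. GRC grouping.** Take three illustrative groups of 35 (counts invented to show the property), as improved / unchanged / worse:
- 20 / 15 / 0: *changed* = (20 + 0)/35 = 57.1%
- 0 / 15 / 20: *changed* = (0 + 20)/35 = 57.1%
- 10 / 15 / 10: *changed* = (10 + 10)/35 = 57.1%

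Three opposite or mixed results give the same value, so the grouped variable has no direction.

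**The case against.** The strongest reply on 1MSTS is that one table cell is blank while the Abstract and the Statistical analysis section both intend a baseline measure. That is right, and a mark lost in reproducing the table cannot be wholly excluded. The loss is therefore conditional on staff following Fig. 1. Even then, a four-visit comparison between randomised arms would remain possible, though it is not the planned analysis.

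On the GRC, the seven-point response is recorded, so direction can be recovered. The four later ratings can be compared between arms, and an unneeded baseline rating loses no data. The mixed model is also conditional on normality and sphericity, so it is not fixed unconditionally for an ordinal item. All of this stands.

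Three stronger readings are tempting, and the protocol does not support them:
- A reader might infer that both outcomes cannot be analysed as planned, full stop. For 1MSTS that holds only under Fig. 1; for the GRC it is the baseline level that fails, not the later visits.
- A reader might attach a loss of precision to the missing 1MSTS baseline. The Statistical analysis section names no baseline covariate, and the protocol gives no baseline-to-follow-up correlation, so no factor can be derived.
- A reader might infer that the *changed* category will be compared between arms. The analysis section lists only the scale and does not say which form enters the model. The grouping may be meant as an anchor for the MCID aim, and a separate analysis plan could settle its use. The category as defined is still without direction in either role.

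**Conclusion.** The point holds as a set of contradictions inside the protocol on two secondary outcomes. If Fig. 1 is followed, 1MSTS has four of the five planned visits, and the change over prehabilitation is lost for every patient so assessed. The GRC has four meaningful visits against five in Fig. 1 and the Statistical analysis section, two item wordings, and a grouped category that cannot show direction.

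The 1MSTS consequence rests on two conditions: that the blank cell is in the protocol as issued, and that staff work from it. The GRC points on timing, wording and grouping follow directly from the text. The analyses of the two primary outcomes, 6MWT and MIP, are not touched. The corrections should be made, and the 1MSTS one promptly, because a missed pre-training value cannot be recovered.

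**What to change.** - In Fig. 1, add the baseline mark for 1MSTS, so that it agrees with the Statistical analysis section and the Abstract.
- In Fig. 1, remove the baseline mark for the GRC. In the Statistical analysis section, take the GRC out of the outcomes measured at baseline and out of the five-visit mixed model.
- Use one item wording throughout, that of the appendix form (function).
- Analyse the GRC at the four post-baseline visits, either as improved / unchanged / worse or ordinally on the recorded scale. Keep improved and worse separate, also where it serves as an anchor for the MCID aim.

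The cost is a corrected table, a few sentences, and a one-minute test at a baseline visit that already takes place. Patients already enrolled without a baseline 1MSTS stay missing; their number should be reported. As changes to study documents, these edits need notification to and approval by the ethics committee, as its approval letter requires.

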## **Sampling and Size Calculation**

The sample size was calculated based on the primary outcome measure (6MWT). A recent systematic review of prehabilitation in patients undergoing major abdominal surgery reported significant improvement in 6MWT, with a mean difference of 29.4 meters (95% CI: 5.6 to 53.3 meters;  $p = 0.02$ ) compared to standard care [31]. The estimated standard deviation was approximately 101.6 meters, corresponding to an effect size (Cohen's  $d$ ) of 0.29. Using this effect size, with  $\alpha$  of 0.05 and power of 80%, the required sample size was calculated to be 54 participants. Allowing for a 30% dropout rate, a total of 70 participants (35 per group) will be recruited. Sample size calculation was performed using G\*Power version 3.1.9.7.

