The level of significance is set at  $p < 0.05$ . Effect sizes will be determined using Cohen's  $d$ , with values of 0.2, 0.5, and 0.8 indicating small, medium, and large effects, respectively [62]. Additional logistic regression will be used to determine preoperative, perioperative and postoperative risk factors associated with the development of respiratory complications. This will be an exploratory analysis, which may identify trends of predictors reported in the literature having an individual effect on postoperative respiratory complications. For all tests conducted, a  $p$  value of  $< 0.05$  (two-sided) will be considered statistically significant, and mean differences (95% CI) will be reported. The results of this study will be reported in accordance with the CONSORT 2010 guidelines.

|                                                                  | STUDY PERIOD                   |                                 |              |                                     |                                               |                                   |                              |
|------------------------------------------------------------------|--------------------------------|---------------------------------|--------------|-------------------------------------|-----------------------------------------------|-----------------------------------|------------------------------|
|                                                                  | Enrolment
& allocation      | Baseline                        | Intervention | Post-
intervention
assessment | Follow up                                     | Follow up                         | Follow up                    |
| TIMEPOINT                                                        | February
2025- July
2026 | 3-5 week
before
operation | 2- 4 weeks   | Preoperatively                      | Post-
operatively
prior to
discharge | 4-6 weeks
post-
operatively | 3 months post
operatively |
| Eligibility screen                                               | X                              |                                 |              |                                     |                                               |                                   |                              |

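### The planned mixed model for 6MWT, MIP and the listed secondary outcomes is used only if normality and sphericity tests pass, so chance can remove the primary analysis and its estimate

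*Protocol*

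**What the plan says.** The Statistical analysis section (Phase 2) lists 6MWT and MIP as primary outcomes. It adds eight secondary outcomes, among them SPPB and the Global Rating of Change Scale. All are to be analysed by a linear mixed-effects model, which the protocol equates with mixed model ANOVA. The model "will be employed, provided the assumptions of normality and sphericity are met". The deciding tests are named: "Normality will be evaluated using the Kolmogorov–Smirnov test, while sphericity will be assessed using Mauchly's test". The 0.05 level is then applied to every test in the section.

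The data come from five visits: "baseline, post-prehabilitation (4 weeks), before hospital discharge, and at 4 and 12 weeks postoperatively". The same section states that "Missing data will be handled using multiple imputation", and promises mean differences with 95% confidence intervals.

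The section does not say whether normality is judged on raw values by arm and visit, on pooled values, or on model residuals. It does not say how many tests must pass, or whether K-S is corrected for an estimated mean and SD. It names no alternative analysis.

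**The concern.** The condition is a rule in the protocol itself, not a detail left open. As written, the primary model is used only if a test computed from the trial's own outcomes does not reject.

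The section promises a mean difference with a 95% interval. The non-inferiority hypothesis (Introduction; section 1.4) needs such an estimate to set against a margin. If the condition fails and, for example, a rank test takes the model's place, that estimate may be lost for reasons unrelated to the treatments.

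Two features make failure likelier than it first appears. Repeated testing across arms and visits rejects normal data by chance. Some listed outcomes also cannot be normal: SPPB is a whole-number score from 0 to 12 (three components of 0 to 4 on the scoring forms), and for the change scale "Responses will be recorded according to a 7-point scale from" very much improved to very much worse.

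The sphericity half is misplaced too. A linear mixed model with a general covariance structure does not assume sphericity.

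**Working it through.** The protocol gives no failure rate, so there is no stated figure to reproduce.

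**Inputs.** Two arms; five visits (Statistical analysis); 35 per arm, since "a total of 70 participants (35 per group) will be recruited"; 27 per arm if only the calculated number is evaluable, since "the required sample size was calculated to be 54 participants" and 54/2 = 27; 0.05 per test. An outcome measured at all five visits has 2 × 5 = 10 arm-by-visit cells.

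**Exactly normal data, by formula.** If k independent tests are each run at 5% and any rejection closes the gate, the failure probability is 1 − 0.95^k.

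- k = 1 (one residual test): 5.0%
- k = 5 (each visit, arms pooled): 1 − 0.95^5 = 22.6%
- k = 10 (each arm and visit): 1 − 0.95^10 = 40.1%
- k = 20 (ten cells for both 6MWT and MIP): 1 − 0.95^20 = 64.2%, an upper figure because the two outcomes are correlated

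**Exactly normal data, by simulation.** Visits within a patient are correlated, so the formula was checked with multivariate normal data, exchangeable correlation 0 to 0.9 and simulated Lilliefors critical values (K-S with estimated mean and SD; D = 0.147 at n = 35 and 0.106 at n = 70).

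| What is tested | Trials failing the gate |
|---|---|
| One residual test | about 5% |
| Five visits, arms pooled (n = 54 or 70) | 19–23% |
| Ten arm-by-visit cells (n = 27 or 35) | 35–41% |
| Ten cells, uncorrected K-S | about 0.1% |

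The last row is low because the uncorrected critical value (D = 0.224 at n = 35) is far too large when mean and SD are estimated. It rejects a normal cell about 0.015% of the time.

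**Discrete outcomes.** The protocol gives no distributions, so these are assumptions: for SPPB, a ceiling-heavy shape, a rounded normal with mean 9 and SD 2, and one with mean 8 and SD 2.5; for the change scale, rounded normals with mean 3 or 4 and SD 1 to 1.5. Cells were simulated as independent.

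| Outcome | Form of K-S | Per cell | Any of ten cells |
|---|---|---|---|
| SPPB | Lilliefors | 33–99% | 98–100% |
| SPPB | Uncorrected | 0.6–41% | 6–99% |
| Change scale | Lilliefors | 72–99.98% | 100% |
| Change scale | Uncorrected | 4–45% | 34–99.8% |

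The change-scale description has four post-baseline administrations, although the schedule also marks baseline. With eight cells the lowest uncorrected figure becomes 1 − (1 − 0.0415)^8 = 28.7%. The lowest Lilliefors figure stays near 100%: 1 − (1 − 0.723)^8.

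**Sphericity half.** Simulated Mauchly tests reject in about 5% of trials under compound symmetry, and in about 100% under an assumed first-order autoregressive correlation of 0.8. Correlation that decays over time is plausible across a surgical course, so this half may close the gate more often than the K-S half.

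**Type I error.** Null trials were simulated with normal data, 35 per arm, correlation 0.5 or 0.8 and the ten-cell Lilliefors gate. Change from baseline to the second visit was compared by t-test, with Mann-Whitney if the gate failed. The gate failed in 38–40% of trials. Type I error was about 5%. Taking the smaller of the two p-values whenever the gate failed raised it to at most 5.4%.

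**The case against.** The strongest reply is that the protocol says only that normality will be evaluated by K-S. It does not say that ten cells are tested, that one failure is decisive, or that the Lilliefors form is used. A single residual test gives about 5%, and uncorrected K-S gives almost nothing. This stands: 40% is the top of a range and not a prediction. But the span from about 0.1% to 41% comes from choices the protocol leaves open while making the outcome of the test binding.

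A second reply is that an SAP may name the fallback. That is fair, and the absent fallback is not the point here. A fallback would not remove the rule that a test on the outcomes selects the primary analysis. The Abstract also gives mixed model ANOVA for the secondary outcomes without any condition, so the two statements differ.

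A reader might infer several stronger things that the documents do not support:

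- That the 0.05 error rate is broken. The null simulation gave about 5%. It covers one fallback and normal data only, but no inflation has been shown.
- That SPPB and the change scale could never be analysed as planned. This holds nearly always under Lilliefors with the assumed shapes, but not under uncorrected K-S.
- That every outcome is gated. HADS is missing from the list in this section.
- That ten cells apply throughout. The schedule marks no baseline for the 1-minute sit-to-stand, and the change scale is described at four occasions.
- That raw scores will be tested, or that the gate will be run on each imputed data set. The text says neither.

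**Conclusion.** The point holds in a limited form. The protocol makes its only named between-arm analysis of 6MWT, MIP and the listed secondary outcomes depend on tests of normality and sphericity. The planned model and its arm difference with 95% interval can therefore be dropped by chance even when the data are ideal.

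The chance from the normality half is about 5%, about 20% or 35–41%, depending on whether one, five or ten tests are run with the Lilliefors form. It is about 0.1% over ten cells with uncorrected K-S. The multi-test figures assume that any one failure closes the gate. The bounded discrete outcomes will often fail, at a rate that depends on their distributions and on the form of K-S. The sphericity half adds a condition that a suitably specified mixed model does not need.

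The harm is uncertainty about which primary analysis and estimate will be reported, not a demonstrated loss of error control. This is a cheap improvement rather than a fatal fault.

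**What to change.** In the Statistical analysis section, delete the whole condition on normality and sphericity, and remove K-S and Mauchly as tests that decide the analysis. Removing only the normality half would leave the model gated. Then state:

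- The linear mixed model is fitted unconditionally for 6MWT, MIP and the other continuous outcomes, with a covariance structure that does not require sphericity (for example, unstructured across visits).
- Residual plots are inspected and reported, but do not select the analysis.
- One sensitivity analysis is fixed in advance, for example a bootstrap confidence interval for the arm difference.
- The Global Rating of Change is analysed either by the changed/unchanged grouping that its own description already defines or by an ordinal model, chosen before outcome data are examined.

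An ordinal model for SPPB is an option but not a requirement, because it would not give the mean differences the section promises.

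The cost is protocol wording and slightly more programming, with no extra patients or visits. Results are not expected until November 2026 (Duration and timeline), so the change should be made before outcome data are analysed.
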